**Research question**

Is serum phosphate an independent predictor of new atherosclerotic cardiovascular disease events in patients stratified by renal function?

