**Study Design**

This will be a retrospective study of the RCGP-RSC cohort. The data available were collected between April 2005 and March 2015 ([name] to confirm). These will be analysed using Read v2 (5-bit) codes to identify patients by the inclusion and exclusion criteria. Laboratory sample data will be taken from the laboratory sample results collected by GP practices.

Inclusion: One or more serum phosphate measurements recorded before a cardiovascular event (primary myocardial infarction; acute coronary syndrome; revascularisation procedure; ischaemic stroke; peripheral vascular disease; vascular dementia), or recorded in patients without any cardiovascular event in the study period. Patients will be aged 18 years and older.

Exclusion: Patients who have already had primary myocardial infarction; acute coronary syndrome or a revascularisation procedure before any serum phosphate measurements have been recorded. Patients with pre-existing ischaemic stroke, peripheral vascular disease or vascular dementia will also be excluded.

Serum phosphate will be a linear variable or analysed further as a categorical variable by range. ‘Time zero’ will refer to the first available serum phosphate measurement of a patient. The time to any outcome measure will be recorded and associations between serum phosphate and outcomes will be analysed by cox-regression.

In patients where more than one serum phosphate measure is available, the mean average of up to the first five measurements from time zero and before any cardiovascular event will be recorded and used in this study.

Importantly, confounding factors for cardiovascular outcomes in all included patients will form part of this study. For each variable, the selected single measurement will be chosen before the outcome measure and as close to time zero as possible, subject to data availability. The exceptions are baseline eGFR and albumin:creatinine ratio – the mean of two measurements in each case will be taken.

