**Intended output**

Outcome measure 1, 2 or 3 – each outcome requires its own table

|  | Outcome X | | |
| --- | --- | --- | --- |
| *Variable* | *Hazard ratio* | *95% CI* | *p value* |
| Age |  |  |  |
| Gender |  |  |  |
| Ethnicity |  |  |  |
| BMI |  |  |  |
| PDDS |  |  |  |
| Smoking |  |  |  |
| Syst. BP |  |  |  |
| HbA1c |  |  |  |
| Tot chol |  |  |  |
| LDL |  |  |  |
| HDL |  |  |  |
| Albumin |  |  |  |
| **Phosphate** |  |  |  |
| Calcium |  |  |  |
| Vit D |  |  |  |
| PTH |  |  |  |
| Sodium |  |  |  |
| Potassium |  |  |  |
| Albumin:Cr ratio |  |  |  |
| Baseline eGFR |  |  |  |

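### Phosphate is averaged over up to five tests with no limit on their span, while the renal adjustment is baseline eGFR, so renal decline in between can leave residual confounding of unknown size

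*Protocol*

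**What the plan says.** All the timing rules are in the protocol's Study Design section.

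- **Origin.** Time zero is the patient's first available phosphate test.
- **Exposure.** Where there is more than one test, the exposure is "the mean average of up to the first five measurements from time zero", restricted to tests before any cardiovascular event. No maximum span is set. Data Source and Sample Size gives an observation period of up to ten years.
- **Covariates in general.** For each one, "the selected single measurement will be chosen before the outcome measure and as close to time zero as possible, subject to data availability".
- **Renal covariates.** "The exceptions are baseline eGFR and albumin:creatinine ratio – the mean of two measurements in each case will be taken". The dates of the two values are not stated.

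The Research question asks whether phosphate is an "independent predictor of new atherosclerotic cardiovascular disease events in patients stratified by renal function". In the Intended output table the renal terms are the albumin:creatinine ratio (ACR) and "Baseline eGFR". The protocol describes no later, date-matched or time-updated eGFR and no eGFR slope. It does not say which eGFR defines the renal strata; the baseline value is the only one it mentions.

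**The concern.** Exposure and main confounder are summarised over different periods. The phosphate mean moves forward from time zero, possibly over years, while the renal term stays at the start. If a patient's eGFR falls during that span and phosphate rises with it, the mean carries information on renal decline that the model does not hold. Decline may itself raise cardiovascular risk, so phosphate can pick up an association that belongs to renal function.

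This bears on the study's central claim, which is independence from renal function. It also affects the strata: a patient classified by baseline eGFR may no longer belong to that stratum when the later phosphate values were drawn.

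**Working it through.** The protocol states no figure on this point, so there is nothing to reproduce. The check has three steps. Every numerical input on renal decline, spacing, slope and test count is an assumption.

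**1. Size of the date mismatch.** With *k* tests spaced *g* years apart, the mean test date is (k − 1)g/2. If eGFR changes by *s* per year, the phosphate mean reflects an eGFR that differs from baseline by s(k − 1)g/2. If phosphate rises by *b* mmol/L per 10 units lower eGFR, and decline has SD σ between patients, the unadjusted decline adds to the phosphate mean an SD of

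(b/10) × σ × (k − 1)g/2.

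- One test: k − 1 = 0, so nothing is added.
- Five tests, weak case (b = 0.01, σ = 1, g = 0.5): 0.001 × 1 × 1 = 0.001 mmol/L.
- Five tests, strong case (b = 0.06, σ = 4, g = 1.5): 0.006 × 4 × 3 = 0.072 mmol/L.

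The other phosphate variation assumed in the first simulation below is √(0.12² + 0.12²/5) = 0.131 mmol/L. The decline component is therefore trivial in the weak case and about half as large (0.072/0.131 = 0.55) in the strong case. Two tests give a quarter, and three tests half, of the five-test displacement. This ignores the cut-off at the event.

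**2. Simulated Cox models with no true phosphate effect.** 40,000 patients, 10 years, about 4,900 to 6,100 events, one run per scenario. Five tests were scheduled for every patient and those after an event were dropped. The log hazard rises 0.2 per 10 units lower current eGFR; b is 0.01, 0.03 or 0.06; g is 0.5 or 1.5 years; mean (SD) eGFR change per year is 0 (0), −1 (1), −1 (2.5) or −2 (4). Baseline eGFR is the mean of two error-prone values at time zero. Entries are hazard ratios (HR) per SD of phosphate.

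| Analysis | No decline (6 scenarios) | Decline (18 scenarios) |
|---|---|---|
| Protocol rule: phosphate mean, baseline eGFR, from time zero | 0.999 to 1.017 | 0.985 to 1.097 |
| Phosphate mean, eGFR averaged over the same dates, from time zero | 0.998 to 1.005 | 0.994 to 1.024 |
| First phosphate, baseline eGFR, from time zero | 1.001 to 1.010 | 0.988 to 1.020 |
| Phosphate mean, baseline eGFR, follow-up from fifth test | 0.990 to 1.021 | 1.000 to 1.338 |
| Phosphate mean, same-date eGFR, follow-up from fifth test | 0.989 to 1.012 | 0.993 to 1.034 |

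Under the protocol rule p was below 0.05 in 5 of the 18 decline scenarios; with same-date eGFR, in none. Scenarios with the same decline share the same simulated events, so 5 of 18 is not an error rate. Under mild decline, −1 (1), the protocol rule gave 0.985 to 1.035. At −2 (4) with b = 0.06 it gave 1.082 and 1.097, against 1.005 and 1.009 with same-date eGFR.

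**3. Effect of test counts.** Two further null simulations kept the origin at the first test.

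- With 60,000 patients, about 8,400 to 8,800 events and b = 0.04: 1.00 to 1.17 with five tests each; 1.00 to 1.06 with one to five tests equally often; 1.00 to 1.03 with half the patients having one test and 10% having five. At a decline SD of 2.5 with yearly tests, the three figures were 1.05, 1.02 and 1.01.
- With yearly tests and decline SD 1.5 to 4: 0.98 to 1.16 with five tests each; 0.98 to 1.05 with mixed counts; 0.98 to 1.03 with date-matched eGFR.

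Together: about 0.98 to 1.17 with five tests each, and about 0.98 to 1.06 with mixed counts.

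**The case against.** The strongest case against is that the effect may be negligible. Inclusion needs only one phosphate test, and such patients cannot contribute. With mixed test counts most simulated hazard ratios are close to 1. This stands as a limit on size. It has a counterweight: the mixed-count runs made test count independent of decline, and the bias would be larger if patients with declining function are tested more often.

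A second objection is that the eGFR dates are inferred. The protocol lists eGFR and ACR as exceptions to the covariate rule and does not date the two values. This also stands. Near time zero is the natural reading of baseline, but it is a reading; on any reading, nothing ties the eGFR values to the phosphate dates.

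Third, date-matching and time-updated covariates are often left to the analysis plan, and the protocol defers modelling to statistical advice. This does not answer the point. The protocol itself fixes how phosphate and the renal covariate are summarised, and the two rules do not match.

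Fourth, the same sentence has a separate problem: it uses exposure values from after time zero and cuts them off at the event. That look-ahead can mask or reverse the renal bias, as the 0.985 suggests, and date-matching alone does not remove it. This stands and shapes the fix.

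A reader might infer that an independent phosphate effect will appear in any group with variable renal decline, or that the largest figures above (up to 1.338) measure the bias in this study. The documents support neither. In 13 of the 18 decline scenarios the protocol rule gave no significant effect. The 1.338 belongs to follow-up from the fifth test, whereas the protocol starts at the first.

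**Conclusion.** The mismatch is in the text and should be corrected. It opens a route by which part of an independent phosphate effect can be residual renal confounding; it does not show that a reported effect would be spurious. With the protocol's time zero and no true effect, the false hazard ratio per SD is about 0.98 to 1.17 if every patient has five tests and about 0.98 to 1.06 with mixed counts. It is small under mild decline and absent in patients with one test or stable eGFR. These ranges rest on assumed decline, spacing, test counts and eGFR-phosphate slope, none of which the protocol gives, and on reading baseline eGFR as near time zero. The true size in this cohort is unknown. With a source population of about 1,250,000 and a 0.05 threshold, even a modest bias could reach significance.

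**What to change.** Amend Study Design in two parts.

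(a) Take phosphate and eGFR, and ACR where available, from one common window ending where follow-up starts. Average eGFR over the dates of the phosphate values used, taking the nearest eGFR to each, and use that eGFR both for adjustment and for the renal strata.

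(b) Also report the analysis with the first phosphate value and the eGFR nearest that date, with follow-up from time zero. This avoids both the date mismatch and the use of exposure values from after time zero.

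The work is protocol wording and date-matching of laboratory records already held, but it has a price. Part (a) loses events that occur before the window ends and phosphate values without a nearby eGFR. Part (b) relies on a single, noisier phosphate value. State the dates of the two eGFR values in either case.

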**Data source and Sample Size**

RCGP-RSC data will be used for this study. These are from a database of coded primary care data from 135 UK General Practitioner (GP) practices – total population of approximately 1,250,000 patients. A large sample size is necessary for this study due to the variability in serum phosphate concentrations and the duration of the observational period (up to ten years).

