**Confounding variables considered**

Demographics: Age (time zero); gender; ethnicity; body weight and height (to calculate body mass index); BMI; postcode-derived deprivation score (PDDS) (UK Index of Multiple Deprivation 2007); smoking status.

Co-morbidities: Cardiovascular disease (primary myocardial infarction; acute coronary syndrome; revascularisation procedure; ischaemic stroke; peripheral vascular disease; vascular dementia); HbA1c; hypertension (SBP).

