**Limitations**

The study population will only include patients that have had sufficient routine blood tests taken. This may introduce bias for increased risk of confounding co-morbidities amongst this group. Serum phosphate levels are influenced acutely and chronically by many factors including disease, exercise and diet - which independently influence cardiovascular risk. We aim to control for cardiovascular risk factors based on the QRISK2 model [6].

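### Confounder values are limited by the outcome date, not by time zero, so some covariates treated as baseline can come from follow-up; the protocol does not allow the bias to be sized

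*Protocol*

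**What the plan says.** Study Design in the protocol fixes the relevant elements. Time zero "will refer to the first available serum phosphate measurement of a patient", and "associations between serum phosphate and outcomes will be analysed by cox-regression". Each confounder is one value, under this rule: "the selected single measurement will be chosen before the outcome measure and as close to time zero as possible, subject to data availability". Baseline eGFR and ACR are named as exceptions, for which "the mean of two measurements in each case will be taken". The two values are not dated, and there is no rule for a patient with fewer than two. Because these are exceptions to the single-value sentence, it is not even clear that its before-outcome limit still covers them.

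Other sections bear on the point:

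- Confounding variables considered ties only age to time zero: "Age (time zero); gender; ethnicity; body weight and height".
- The Research question concerns "new atherosclerotic cardiovascular disease events in patients stratified by renal function", so eGFR has a second role as a stratifier.
- Data source and Sample Size allows an observation period of as much as ten years.
- Limitations accepts that "The study population will only include patients that have had sufficient routine blood tests taken", but does not mention covariate values recorded after time zero.
- No section provides for a landmark, delayed entry or time-varying covariates.

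**The concern.** A Cox model with fixed covariates should use what is known when the clock starts. Here the rule looks forward as far as the outcome, which raises two problems for patients who lack a value (or two values, for eGFR and ACR) by time zero.

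- **Availability depends on staying event-free.** A patient with an early event has little time to acquire the value. A patient without an event has until the end of follow-up. If patients with incomplete covariates are dropped, cases are lost more often than non-cases. If testing is also related to phosphate, the phosphate hazard ratio is distorted.
- **The value may be a consequence.** An eGFR, ACR, PTH or systolic pressure recorded during follow-up may reflect phosphate or declining kidney function. Adjusting for it may remove part of the association under study, and an eGFR from follow-up would also place the patient in a renal stratum.

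**Working it through.** The protocol states no event count, effect size or power, so there is no figure to reproduce. The check is a reading of the rule followed by simulations. Every numerical input below is an assumption, except the ten-year maximum.

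**1. Who is affected.** A patient with the required values by time zero can supply them from that period, so their availability does not depend on survival. A patient without them is sent into follow-up, with no maximum distance from time zero.

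**2. Unequal opportunity.** Suppose a missing single value arrives at 0.3 per year. The chance of having it by time t is 1 - exp(-0.3t). For two values with a mean gap of 2 years each, the chance is 1 - exp(-t/2)(1 + t/2).

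| Event or censoring at | One value | Two values |
|---|---|---|
| 1 year | 0.26 | 0.09 |
| 5 years | 0.78 | 0.71 |
| 10 years | 0.95 | 0.96 |

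**3. Single-value simulation.** Inputs: 20,000 patients, 10 replicates, event rate 0.015 per year, follow-up uniform over 0-10 years, true phosphate hazard ratio (HR) 1.00 per SD. Patients without a value by time zero are first measured at 0.3·exp(b·z) per year, where z is standardised phosphate. Patients with no value before event or censoring are dropped.

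| Value by time zero | b | HR, full cohort | HR, complete cases | HR, delayed entry | Patients lost | Events lost |
|---|---|---|---|---|---|---|
| 80% | 0 | 0.994 | 0.995 | 0.995 | 6.8% | 9.4% |
| 80% | 0.3 | 1.003 | 1.006 | 1.004 | 6.9% | 9.1% |
| 80% | 0.6 | 1.008 | 1.012 | 1.008 | 7.1% | 9.2% |
| 50% | 0 | 0.996 | 1.005 | 1.004 | 16.9% | 23.1% |
| 50% | 0.3 | 1.002 | 1.008 | 0.998 | 17.0% | 22.8% |
| 50% | 0.6 | 0.979 | 0.989 | 0.971 | 17.6% | 23.5% |
| 20% | 0 | 1.008 | 1.007 | 1.009 | 27.1% | 37.3% |
| 20% | 0.3 | 1.006 | 1.047 | 1.010 | 27.2% | 36.4% |
| 20% | 0.6 | 1.015 | 1.072 | 1.007 | 28.2% | 36.8% |

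Simulation error: the event probability is 1 - (1 - exp(-0.15))/0.15 = 0.071, or about 1,430 events per replicate. The standard error of the mean log HR is about 1/√14,300 = 0.008. Complete cases should therefore be read against the full cohort in the same row. The two largest ratios are 1.047/1.006 = 1.04 and 1.072/1.015 = 1.06. With b = 0 the complete-case HR was 0.995 to 1.007, so there is no material bias. Events are lost more often than patients in every row.

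**4. Two-value simulation (eGFR and ACR).** The second value arrives after two exponential gaps, each of mean 0.5-2 years, multiplied by exp(-k·z) with k = 0.2 or 0.4. Incomplete cases are dropped and there is no true effect.

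- Testing depends directly on phosphate, nobody has earlier values (120,000 patients, 4 replicates): HR 1.05-1.17, with 43-80% of cases kept against 59-89% of non-cases. A repeat with 60,000 patients and 6 replicates gave 1.04-1.18.
- Same, but half already have both values: HR 1.01-1.04.
- Testing depends on kidney function (correlation 0.4 with phosphate), which is in the model; nobody has earlier values (60,000 patients, 6 replicates): HR 0.98-1.00, within 0.004 of the full cohort.
- Same, with kidney function measured with error (SD 0.3): HR 1.01-1.03, at most 0.017 above the full cohort; Monte Carlo standard error about 0.01.

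**5. Not quantified.** The effect of adjusting for a consequence of phosphate was not simulated. It could pull towards no association, the opposite direction to the inflation in step 4.

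**The case against.** There are good arguments in favour of the plan.

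- **The rule asks for nearness to time zero.** A distant value is used only when no nearer one exists, and values before time zero are allowed. This stands, and it limits the problem to patients without such values. It sets no bound for them.
- **No complete-case rule is stated.** Inclusion needs one phosphate value, and a SAP, not available here, may deal with missing covariates. This stands against the selection figures, all of which drop incomplete cases. It does not rescue the timing rule: a value taken from follow-up is not missing under that rule, so imputation would leave it in place.
- **Kidney function is in the model.** If it drives testing, the phosphate HR is largely protected. Step 4 bears this out. The larger figures need testing to depend on phosphate beyond kidney function, which nothing in the protocol establishes.
- **A strict cut-off creates missing data** for patients whose first phosphate falls near the start of the data. This stands and belongs in the cost of the change.

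A reader might infer that the planned phosphate HR is inflated by 5-18%, or that every patient's covariates depend on survival. The documents support neither. The first needs three conditions together: nobody with earlier values, testing tied directly to phosphate, and incomplete cases dropped. The second ignores patients who already have their values by time zero.

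**Conclusion.** The timing rule is stated in the protocol and is flawed as stated; it is not a detail left for later. Followed exactly, it can put follow-up values into the adjustment and into the renal strata. It should be corrected before extraction, but the protocol does not show that the primary result would be materially wrong.

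The size and net direction of the bias cannot be found from the protocol, because the share of covariates recorded after time zero, the determinants of testing and the handling of missing values are not given. Under assumed inputs and complete-case analysis, the spurious phosphate HR per SD runs from close to 1.00 (testing driven by modelled kidney function), through about 1.00-1.04 (half with earlier values), to about 1.05-1.18 (nobody with earlier values and testing tied directly to phosphate). Selection and over-adjustment may act in opposite directions.

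**What to change.** Replace the timing sentence in Study Design with a rule anchored on time zero:

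- For each confounder, use the recorded value closest to, and not later than, time zero.
- For eGFR and ACR, average the two most recent values on or before time zero, or use one if only one exists. Apply the same rule when forming the renal strata.
- Treat absent values as missing, for example by multiple imputation, and do not fill them from follow-up.
- Keep the present rule, or delayed entry at the date of the last required value, as a sensitivity analysis.

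The data are retrospective, so only the extraction rule changes. The cost is more missing covariates, especially for patients whose first phosphate falls soon after the data start in April 2005 (a date that the protocol marks for confirmation). Missingness should therefore be reported by calendar year of time zero.

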**Confounding variables considered**

Demographics: Age (time zero); gender; ethnicity; body weight and height (to calculate body mass index); BMI; postcode-derived deprivation score (PDDS) (UK Index of Multiple Deprivation 2007); smoking status.

Co-morbidities: Cardiovascular disease (primary myocardial infarction; acute coronary syndrome; revascularisation procedure; ischaemic stroke; peripheral vascular disease; vascular dementia); HbA1c; hypertension (SBP).

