**Primary Outcome Measure**

Composite cardiac (atherosclerosis) cardiovascular disease outcome measure of primary myocardial infarction; acute coronary syndrome; revascularisation procedure.

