**Statistical analysis**

Numerical data will be refined by excluding values beyond physiological limits. Data will be analysed using the statistical package R, with P values <0.05 being regarded as statistically significant. Expert statistical advice will be sought with the aim of using cox regression models to determine the association between serum phosphate and cardiovascular events, adjusting for the known cardiovascular risk factors. Cox proportional hazards multivariate models will also be constructed to provide a time-event analysis. A backwards stepwise elimination of variables approach will help to refine the model and evaluate the contribution of each variable towards the outcome measures.

Ethical considerations

Approval has been sought from the RCGP for the RSC database to be used for such research projects. Our study is retrospective and observational over anonymised patient data. The study involves no clinical interventions, no patient contact and no breach of confidentiality. The results of the study will be submitted for publication to a peer-reviewed journal.

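### The confounder list includes six cardiovascular conditions that are excluded at time zero and used as the outcomes, so the covariate is either constant or a post-baseline study event

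*Protocol*

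**What the plan says.** The Protocol gives the same six conditions three roles.

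- **Outcomes.** The primary outcome is the "Composite cardiac (atherosclerosis) cardiovascular disease outcome measure of primary myocardial infarction; acute coronary syndrome; revascularisation procedure". The secondary outcomes are its three components taken singly. The tertiary outcomes are ischaemic stroke, peripheral vascular disease and vascular dementia, also taken singly.
- **Exclusions (Study Design).** The protocol excludes "Patients who have already had primary myocardial infarction; acute coronary syndrome or a revascularisation procedure before any serum phosphate measurements have been recorded", and adds: "Patients with pre-existing ischaemic stroke, peripheral vascular disease or vascular dementia will also be excluded". Time zero is the patient's first available phosphate result.
- **Confounders (Confounding variables considered).** The co-morbidity line opens with "Co-morbidities: Cardiovascular disease (primary myocardial infarction; acute coronary syndrome; revascularisation procedure; ischaemic stroke; peripheral vascular disease; vascular dementia" and then names HbA1c and hypertension (SBP).

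Study Design says that "confounding factors for cardiovascular outcomes in all included patients will form part of this study". Its timing rule for every covariate is that "the selected single measurement will be chosen before the outcome measure and as close to time zero as possible, subject to data availability". Statistical analysis plans Cox models "adjusting for the known cardiovascular risk factors", refined by backward elimination. The Intended output table has 20 rows, phosphate among them, and none for cardiovascular disease.

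**The concern.** A confounder has to vary between patients at baseline. After the exclusions this one does not. If an analyst nevertheless builds a variable that does vary, it must come from events after time zero, and every such event is one of the study's own endpoints.

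That matters in two ways. If phosphate raises the risk of all these events, adjusting for one of them when modelling another can remove part of the association under study. And coding a later event as though it were known at time zero gives the flagged patients a guaranteed event-free interval, so the flag's own hazard ratio is distorted.

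**Working it through.** The protocol states no figure on this point, so there is none to reproduce. The check is a cross-reading, followed by simulations to gauge size.

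**Step 1: value at time zero.** All six conditions are exclusions before the first phosphate result. The covariate is 0 for every included patient, its variance is 0, and its coefficient cannot be estimated. The item's parenthesis names exactly these six, so no other cardiovascular history that could vary at baseline is defined.

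**Step 2: what the timing rule lets in.** A value must precede the outcome and be as near time zero as possible. It need not fall at or before time zero.

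| Model | What could enter under the rule |
|---|---|
| Composite | An earlier stroke, peripheral vascular disease or vascular dementia. The composite ends at its first component, so no component can precede it. |
| Single outcome | Any of the other five, if earlier; for example acute coronary syndrome coded just before infarction |

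**Step 3: size if the other event is independently timed.** Every input here is an assumption, not a protocol figure.

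- *Run A:* 20,000 patients, 10 years, each event type at 1% per year, true phosphate hazard ratio 1.20 per SD, 1,862 events. The phosphate ratio was 1.21 without the flag and 1.22 with it. The flag's ratio was 0.54 although its true effect was null, which is the immortal-time artefact. The standard error of its log was 0.10, so z = ln(0.54)/0.10 = −0.62/0.10 ≈ −6.2. Backward elimination at 0.05 would keep this spurious term.
- *Run B:* 40,000 patients, 4 replicates, infarction 0.6% and other events 1.2% per year, true ratio 1.18, flag strictly before infarction, with shared frailty added.

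| Frailty (log-SD) | Without flag | With flag | Shift |
|---|---|---|---|
| none | 1.166 | 1.174 | +0.008 |
| 1 | 1.163 | 1.160 | −0.003 |
| 1.5 | 1.157 | 1.142 | −0.015 |

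- *Run C:* a further run with an independently timed earlier event gave 1.167 without the flag and 1.180 with it, a shift of +0.013.

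**Step 4: size if another code sits close to the infarction.** The share of infarctions carrying such a code is assumed.

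| Simulation | Overlap | Without flag | With flag | Cut | Fall in log HR |
|---|---|---|---|---|---|
| Code just before infarction | 30% | 1.16 | 1.12 | 0.04 | 1 − 0.113/0.148 = 24% |
| Code just before infarction | 60% | 1.19 | 1.08 | 0.11 | 1 − 0.077/0.174 = 56% |
| Other code recorded, order not imposed (120,000 patients) | 30% | 1.180 | 1.121 | 0.059 | 1 − 0.114/0.166 = 31% |
| Other code recorded, order not imposed (120,000 patients) | 60% | 1.180 | 1.066 | 0.114 | 1 − 0.064/0.166 = 61% |

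Only the first two rows respect the timing rule; the last two are shown for comparison. Across both, the cut is about 0.05 at 30% and 0.11 at 60%. On the log scale the loss is close to the overlap share.

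**The case against.** The strongest reply is that the models may never contain this covariate. The section heading speaks of variables considered, and the output table has no cardiovascular row. Limitations says that control will follow the QRISK2 model. The same list names weight and height only as ingredients of BMI, so it serves at least partly as an extraction list, and the cardiovascular codes have to be extracted for eligibility and outcomes anyway. If the variable is read strictly at time zero, it drops out and leaves the phosphate estimate untouched. It is also open whether a rule about a selected single measurement governs diagnosis codes at all. All of this stands, and it limits the weight of the point. It does not reconcile the list with the exclusions and the table.

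A reader might infer more: that the composite is adjusted for its own components, or an outcome for itself. A flag for any of the six events at any time in the study does wreck the model. Under Run A's inputs the fit failed to converge and the phosphate ratio fell from 1.21 to 1.02. The documents do not support that reading, because the rule asks for values before the outcome. Nor do they support a claim that attenuation is certain: with independently timed events, the shift was 0.015 or less in either direction.

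Two limits remain. The runs in Step 3 do not represent near-simultaneous coding, which is where the attenuation arises. And the non-cardiac exclusion gives no explicit time anchor for pre-existing disease, although before time zero is its natural meaning.

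**Conclusion.** The point holds as an internal inconsistency, with a real but conditional analytic risk. The confounder list conflicts with the exclusions and with the output table. The listed item is either constant or a post-baseline study event, and neither is a legitimate baseline confounder.

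The effect on the phosphate hazard ratio runs from negligible to a cut of roughly 0.05 to 0.11 from a value near 1.18. The upper range requires 30% to 60% of infarctions to carry another cardiovascular code just before the event; these shares, and all event rates used, are assumptions. The larger cuts concern the infarction model. For the composite, only an earlier non-cardiac event could enter, and no comparable attenuation has been shown there. The correction is worth making because it is nearly free and closes off over-adjustment. The documents do not show that the planned primary estimate is biased.

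**What to change.** In Confounding variables considered, remove only the cardiovascular disease item and its parenthesis from the co-morbidity line. HbA1c and hypertension (SBP), on the same line, stay; both appear in the output table. Then add a sentence to Study Design or Statistical analysis such as: no cardiovascular event occurring after time zero will enter any model as a fixed covariate. If the authors meant some other cardiovascular history, they should define one that is neither an exclusion nor an outcome.

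The cost is one deletion and one sentence. The six conditions are still extracted for eligibility and outcomes, and the output table needs no change. A sensitivity analysis censoring at the first event of another type is optional and not part of this correction.
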